#### Inter-Rater Reliability

The inter-rater reliability of the exercise type and technique (human-assigned) labels will be evaluated using Fleiss kappa from the independent ratings of the treating physiotherapist recorded at the time of data collection and 2 research physiotherapists following a video review.

#### Univariable and Multivariable Analyses

The relationship between adherence (dependent variable) and individual baseline adherence predictor variables and environment (home or clinic) will be examined using parametric univariable statistical analyses, linear regression for continuous predictors, and 2-sample *t* tests and analysis of variance for binary and multiclass categorical predictors. A multivariable analysis will be conducted to model adherence from statistically significant predictors (maximum 12) and evaluate their relative importance.

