##### Hypotheses

The related hypotheses are as follows:

Exercise technique adherence is better for supervised sessions than at home (*P*<.05).There will be a statistically significant association (*P*<.05) between home physiotherapy exercise participation and technique adherence and the identified clinical outcomes.

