#### Inertial Data Collection

Each study subject will be provided with a smart watch to be worn on their affected extremity when performing the prescribed physiotherapy exercise. The smart watch must be worn for all physiotherapy exercise sessions conducted over the duration of treatment, up to a maximum of 5 months. This includes all supervised physiotherapy sessions at the Holland Centre and any physiotherapy exercise sessions conducted by the patient independently (home exercises). No alteration to the prescribed physiotherapy will be undertaken during this clinical validation study.

The smart watches purchased for this study will have a 9-axis IMU (3-axis accelerometer, 3-axis gyroscope, and 3-axis magnetometer). The inertial sensors will be sampled at 50 Hz and recorded to the internal memory storage on the smart watch. The inertial data will be encrypted using the Rivest–Shamir–Adleman public-key cryptosystem. The smart watch will permit up to 150 hours of sensor data recording to its 4 GB internal memory. The sensor data will be retrieved and removed from the smart watch when the patient attends supervised physiotherapy at the Holland Centre (2 times per week).

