#### Smart Physiotherapy Activity Recognition System-Home Physiotherapy Technique Adherence

A second supervised learning algorithm will be trained, validated, and optimized to classify the exercise technique from the labeled inertial sensor data collected during the supervised physiotherapy sessions. We anticipate that a CRNN architecture similar to the exercise type classifier will likely be suitable. The validated technique classifier will be used to evaluate the technique adherence from the inertial data collected during unsupervised home sessions.

Anticipated challenges with the proposed supervised learning approach to technique evaluation include class imbalance and recovery-related changes in exercise performance. It is anticipated that many more correct technique training examples may be available for some exercises and that an exercise may be performed incorrectly in ways not observed during the supervised sessions, leading to class imbalance. It is also anticipated that through recovery, the expectation for technique and performance of an exercise may change over time, creating a moving target for the technique classifier. The challenge of class imbalance may be mitigated using several potential approaches including (1) random over and undersampling [117]; (2) cost-sensitive learning [117]; (3) semisupervised learning [118]; (4) anomaly detection [119,120]; and (5) synthetic data augmentation [121]. The challenge of recovery-related performance changes may be mitigated by providing our technique classifier metadata related to the classification task (eg, treatment week, pathology, and surgery) [116], implementing patient-specific ML models using transfer learning, and periodically retraining the ML models through recovery.

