### Data Analysis

#### Sample Size

The proposed sample size of 120 for clinical validation yields a power of 80% to detect weak correlations (*R*>0.25) between physiotherapy adherence and clinical outcomes, accepting a 5% alpha error. Sample size feasibility was confirmed by the WCP, anticipating a recruitment rate of 70%. The pilot study sample size (20) was used to detect implementation challenges with an incidence rate greater than 15% at a 95% confidence level [124] (not statistically significant differences in clinical or economic outcomes).

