#### Concurrent Validity

Concurrent validity of SPARS will be established with (1) patient home exercise adherence diaries; and (2) physiotherapist exercise logs recorded in the absence of the researchers. The number and type of exercises measured by SPARS will be evaluated against both the adherence diaries and physiotherapist logs. The evaluations of the SPARS technique will be compared with the physiotherapist logs. Systematic bias between measurement methods will be evaluated using a paired sample *t* test and Bland-Altman plots [125]. Reproducibility will be evaluated using an intraclass correlation with a 2-way random-effects model for absolute agreement interclass correlation coefficient (2,1) [126].

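### Environment (home or clinic) falls under a 2-sample t test although each patient supplies both settings, so the supervised-versus-home hypothesis is tested with the wrong standard error

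*Protocol article*

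**What the plan says.** Aim 2 of the Protocol article states two hypotheses. The first, under Hypotheses, is: "Exercise technique adherence is better for supervised sessions than at home", to be judged at P<.05.

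The only analysis text that covers the home or clinic setting is Univariable and Multivariable Analyses. There adherence is the dependent variable, and its relation to "individual baseline adherence predictor variables and environment (home or clinic) will be examined using parametric univariable statistical analyses". Linear regression is for continuous predictors; the categorical ones get "2-sample *t* tests and analysis of variance for binary and multiclass categorical predictors".

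Inertial Data Collection describes who supplies the data. Every subject wears the watch for all exercise sessions during treatment: "This includes all supervised physiotherapy sessions at the Holland Centre and any physiotherapy exercise sessions conducted by the patient independently (home exercises").

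A paired test appears once, under Concurrent Validity, for another purpose: "Systematic bias between measurement methods will be evaluated using a paired sample *t* test and Bland-Altman plots".

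**The concern.** Baseline variables such as sex or smoking status divide patients into separate groups, and a 2-sample t test suits a binary one. Environment does not divide patients. The same people are observed in both settings, and a patient with good technique in the clinic probably tends to have good technique at home. A 2-sample test ignores that correlation, so its standard error does not describe the sampling variation of the difference.

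At stake is one of only two stated hypotheses. The Introduction (Are Home Shoulder Physiotherapy Exercises Performed Correctly?) presents it as a question that no study has answered. The sample-size statement concerns correlations between adherence and outcome, so no stated calculation covers this comparison.

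**Working it through.** **The plan's own figure.** Sample Size states: "The proposed sample size of 120 for clinical validation yields a power of 80% to detect weak correlations" (R>0.25, 5% alpha). With a two-sided test and Fisher's z, power = Φ(atanh(0.25) × √117 − 1.96) = Φ(2.763 − 1.960) = 78.9%. The noncentral t gives 80.1%. The figure reproduces, but for a correlation and not for the home-versus-clinic difference.

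**Inputs for the comparison**
- From the document: n = 120 and alpha 5%. Sidedness is not stated; two-sided is taken because it fits the plan's own figure.
- Assumed, because the document gives no value: within-patient correlation ρ = 0.5 (range 0.3 to 0.7) and SD = 20 percentage points in each setting. The analysis unit is one mean per patient per setting.

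**Standard errors**
- 2-sample: SD × √(2/n) = 20 × √(2/120) = 2.58.
- Correct for paired data: SD × √(2(1−ρ)/n) = 20 × √(1/120) = 1.83 at ρ = 0.5.
- Ratio: 1/√(1−ρ), which does not depend on the SD.

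**Type I error** of the nominal 5% 2-sample test: 2 × (1 − Φ(1.96 × ratio)).

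**Power** of the 2-sample test at the difference where the paired test has 80%: Φ(1.960 + 0.842 − 1.960 × ratio).

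| ρ | SE ratio | True type I error | 2-sample power where paired has 80% |
|---|---|---|---|
| 0.3 | 1.20 | 1.9% | 68% |
| 0.5 | 1.41 | 0.6% | 51% |
| 0.7 | 1.83 | 0.03% | 22% |

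A simulation of 20,000 trials at ρ = 0.5 gave a type I error of 0.7% for the 2-sample test and 5.0% for the paired test.

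**Detectable difference at 80% power, SD 20, ρ = 0.5**
- Paired: (1.960 + 0.842) × 1.83 = 5.1 points.
- 2-sample: the critical value uses the wrong SE, but the estimate still varies with the correct one. So 1.960 × 2.58 + 0.842 × 1.83 = 5.06 + 1.54 = 6.6 points. Multiplying 2.802 by 2.58 would give 7.2 and overstate the loss.

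**If repeated rows are entered as independent.** Participation adherence is defined per 2-week interval, and 5 months hold about 10 intervals. Assume k = 10 rows per patient per setting, and split the total variance into a patient share a, a patient-by-environment share b and a residual share e = 1 − a − b. Naive SE / true SE = 1/√(kb + e).
- a = 0.5, b = 0: 1/√0.5 = 1.41, type I error 0.6%.
- a = 0.3, b = 0.1: 1/√1.6 = 0.79, type I error 12%.
- a = 0.3, b = 0.2: 1/√2.5 = 0.63, type I error 22%.

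The direction of the error thus depends on the unit of analysis, which the text does not fix for environment.

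**The case against.** **The sentence is condensed and may not mean this.** It covers all baseline predictors plus environment and names neither the hypothesis nor technique, so the pairing of environment with the 2-sample test is inferred. That is true, but it is the literal reading, and no other section offers a test for environment. Concurrent Validity shows that the authors distinguish a paired from a 2-sample test. Nor is this a detail left to an analysis plan: the protocol names a test, and it does not suit the design.

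**The error is harmless because it is conservative.** With patient means and positive correlation this stands in part. With complete pairs the estimated difference is unchanged, and false support for the hypothesis becomes rarer. The cost is power. The defence fails if intervals or sessions are the rows.

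**A stronger reading about measurement.** Clinic technique is labelled by the treating physiotherapist (Inertial Data Labeling). For home technique the plan says: "The validated technique classifier will be used to evaluate the technique adherence from the inertial data collected during unsupervised home sessions". A reader might infer that the two sides are scored differently, so that classifier error alone would create a gap in favour of the hypothesis. The document does not support this:
- No section makes the physiotherapist's labels the clinic comparator; they are described as training and validation data.
- Concurrent Validity compares SPARS technique evaluations with physiotherapist logs made without the researchers present. This requires classifier scores on supervised sessions that had no synchronous labels.
- The participation section likewise applies the trained algorithms to such sessions. With two supervised sessions a week and labelling once every 2 weeks, about three of every four are unlabelled.
- Construct Validity plans by-session cross-validation, which yields out-of-fold predictions for the labelled sessions.

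If one classifier with the same error rates scores both settings, it creates no gap where none exists. What remains is that no sentence says these scores form the clinic side of the comparison.

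**Conclusion.** The concern holds for the test. As written, the only analysis covering environment treats one set of patients as two independent groups, and the standard error is wrong unless the within-patient correlation is zero and patient means are used.

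On patient means the consequence is lost power, not false positives. How much is lost depends on the correlation, which the document does not give. The loss in points also depends on the assumed SD of 20, and no target difference is stated against which to judge a rise from about 5.1 to about 6.6 points. The anticonservative case is a possibility under assumed variance shares, not something the plan prescribes.

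On measurement, only a clarification is warranted. The document does not establish a bias toward the hypothesis.

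**What to change.** In Univariable and Multivariable Analyses, take environment out of the list of baseline predictors and give it its own analysis, with the unit of analysis stated. Either of these would do:
- a paired t test on each patient's mean technique adherence in each setting; or
- a mixed model with a patient random effect and environment as a within-patient factor.

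The paired test is simpler but drops any patient with data in only one setting, for example someone who records no home exercise. The mixed model keeps such patients. If interval-level or session-level rows are used, the model should also allow the home-clinic difference to vary between patients, since that variance component drives the anticonservative case.

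Add one sentence stating that the clinic side uses SPARS technique scores from unlabelled supervised sessions, or out-of-fold scores from labelled ones, so that the same classifier scores both settings on data outside its training.

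The cost is a change of wording and no new data. The one extra task is to keep the out-of-fold predictions if labelled sessions are to be included.

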### Home Physiotherapy for Rotator Cuff Pathology

There is little comparative data on the relative effectiveness of supervised physiotherapy versus home-based exercise for rotator cuff pathology [3,24]. Although several trials have sought to address this question [34,40-42], all were of low sample size and adherence to the prescribed physiotherapy was not measured. The efficacy (or lack thereof) of a self-management strategy can only be determined if it is adhered to, which requires measurement of adherence. These studies also used different exercise regimens for their study groups, with the group in supervised therapy receiving a more extensive, specific, and individualized exercise regimen. To our knowledge, no study has directly compared the supervised and independent performance of the same rotator cuff rehabilitation protocol or sought to determine the optimal balance between supervised and independent exercise in hybrid programs. Despite these limitations, the efficacy of independent exercise for rotator cuff rehabilitation is supported by many studies with good outcomes that made extensive use of home exercise in their rehabilitation protocol [3,7,8].

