#### Inertial Data Labeling

The researchers will attend a supervised physiotherapy session for each patient once every 2 weeks to record exercise type and technique labels synchronously with inertial data collection, based on the input from the treating physiotherapist. The technique will be labeled as a binary variable, indicating if the treating physiotherapist was satisfied that the exercise was performed correctly (as intended). The treating physiotherapist will also make a record of prescribed home exercises and exercise type and technique evaluations at each supervised physiotherapy session.

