#### Barriers to Adherence

The following potentially significant adherence predictors [12,105-110] will be collected for each patient at recruitment: age, sex, body mass index, dominant side involvement, symptom duration, mechanism of injury (traumatic or degenerative), rotator cuff tear thickness and size, type of operative procedures, comorbidity (cumulative illness rating scale [111]), smoking status, alcohol intake, opioid intake, cannabinoid intake, the baseline level of physical activity, education, marital status, job demands, socioeconomic status (current income), perceived social support (Enhancing Recovery in Coronary Heart Disease Social Support Inventory [112]), patient self-efficacy (2-item Pain Self-Efficacy Questionnaire [113]), Patient Expectation Questionnaire [114], and Hospital Anxiety and Depression Scale [115].

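### The home-versus-clinic technique comparison is univariable and does not hold exercise type fixed, so a different exercise mix in the two settings could create, hide or reverse the difference

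*Protocol article*

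**What the plan says.** The first of the two Aim 2 hypotheses reads: "Exercise technique adherence is better for supervised sessions than at home", at P<.05. Technique is a correct-or-not judgement (Inertial Data Labeling: "The technique will be labeled as a binary variable").

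The analysis is in Univariable and Multivariable Analyses. Adherence is the dependent variable, and "environment (home or clinic) will be examined using parametric univariable statistical analyses", with "2-sample *t* tests and analysis of variance for binary and multiclass categorical predictors". Environment has two levels, so the stated test is a 2-sample t test. The multivariable step then models adherence from the predictors found significant, up to 12. Apart from environment, the candidates are the variables listed in Barriers to Adherence, which "will be collected for each patient at recruitment". Exercise type and treatment week are not on that list.

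Two other places matter:
- The section on technique adherence (Methods) anticipates that, for some exercises, correct examples may far outnumber incorrect ones. It also anticipates that what is expected of an exercise may shift during recovery. Its remedies (resampling, metadata such as treatment week, retraining) are for the classifier, not for this comparison.
- Inertial Data Labeling says: "The treating physiotherapist will also make a record of prescribed home exercises and exercise type and technique evaluations at each supervised physiotherapy session". Home prescriptions and clinic exercises are thus both recorded, but nothing requires them to occur in the same proportions.

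**The concern.** The introduction asks whether motion patterns trained under supervision are kept up at home. That is a question about the same exercise done in two places. A univariable contrast answers a different one: whether the overall share of correct technique differs between whatever was done in the clinic and whatever was done at home.

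If some exercises are harder to do correctly, and the settings contain them in different proportions, the crude contrast mixes the effect of supervision with the effect of exercise choice. Pairing each patient's home and clinic scores does not remove this, because both scores in the pair carry the mix. Adjusting for recruitment variables does not remove it either, because those do not vary between a patient's home and clinic sessions. At stake is the reading of one of the two formal hypotheses of the cohort study.

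**Working it through.** **The plan's own figure.** The only power statement for the cohort is 80% for a correlation of 0.25 with 120 patients at 5%. By Fisher z, Φ(atanh(0.25) × √117 − 1.96) = Φ(0.803) = 78.9%; by noncentral t it is 80.1%. The figure reproduces, but it concerns adherence and clinical outcomes, not this hypothesis.

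**Inputs.** From the article: 120 patients, a binary technique label and 5% alpha (two-sided assumed). Assumed, because the article gives none: rates of correct technique, exercise mixes and between-patient spread.

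**Formula.** Take two exercise groups, easy and hard, with the same true clinic-minus-home gap in each:

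crude difference (clinic − home) = true gap + (hard share at home − hard share in clinic) × (easy rate − hard rate)

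| Easy / hard % correct (clinic) | True gap | Hard share clinic / home | Clinic % | Home % | Crude difference | Effect of mix |
|---|---|---|---|---|---|---|
| 90 / 70 | 0 | 50 / 30 | 80.0 | 84.0 | −4.0 | creates |
| 95 / 70 | 0 | 30 / 50 | 87.5 | 82.5 | +5.0 | creates |
| 95 / 70 | +5 | 50 / 50 | 82.5 | 77.5 | +5.0 | none |
| 95 / 70 | +5 | 50 / 30 | 82.5 | 82.5 | 0.0 | hides |
| 95 / 70 | +5 | 50 / 20 | 82.5 | 85.0 | −2.5 | reverses |
| 90 / 80 | +5 | 70 / 30 | 83.0 | 82.0 | +1.0 | mostly hides |

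With exercise type held fixed, every row returns its true gap.

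**How often a spurious shift would reach P<.05 in a correctly paired test.** Normal approximation, no true effect, SE = SD/√120:
- 4 points (90% and 70%; 50:50 against 70:30). Paired SD 15: SE 1.37, Φ(2.92 − 1.96) = 83%. Paired SD 25: SE 2.28, Φ(1.75 − 1.96) = 42%.
- 6 points (90% and 60%, same mixes): 99% and 75%.
- 2 to 3 points (home mix only 60:40): between 14% and 59%.

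**The test as written.** A simulation used 120 patients, 100 rated repetitions per setting, between-patient SD 8 points, 95% and 70% correct, and 2,000 runs:

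| True gap | Hard share clinic / home | 2-sample t test | Paired t test |
|---|---|---|---|
| 0 | 50 / 50 | significant in 0% | significant in 5.4% |
| 0 | 30 / 50 | clinic better in 100% | clinic better in 100% |
| 0 | 50 / 30 | home better in 100% | home better in 100% |
| +5 | 50 / 30 | clinic better in 0% | clinic better in 0.5%, home better in 10.5% |
| +5 | 60 / 20 | home better in 100% | home better in 100% |

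The values near 100% reflect the small assumed noise and should not be read as forecasts. The useful result is the pattern: with equal mixes pairing gives close to the nominal 5%, but with unequal mixes it does not protect.

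**The case against.** The strongest reply is that nothing in the article says the mixes differ. Recording home prescriptions and leaving treatment unaltered do not imply different proportions. Divergence is also limited, because the classifier learns only exercise types labelled in the clinic, so a type never labelled there cannot be recognised at home. All this stands: the size is unknown and may be zero. But proportions can still differ, and the planned test could not show whether they had.

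A second reply is that the article does not say how a technique score is built, and that adjustment belongs in a fuller plan not shown. This stands in part: pooling over exercises is the natural reading, not a stated rule. The univariable test, however, is stated, and it is the only home-versus-clinic test given. A fuller plan that stratifies by exercise would have to depart from it.

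Three stronger readings are tempting, and the article does not support them:
- *A reader might infer a timing bias, with technique rising through recovery while home activity falls.* The article says only that the expectation for technique and performance may shift. The label records whether the exercise was done as intended at that session, so no trend in percent correct follows. Falling home volume is not stated either.
- *A reader might see the weakness that the introduction finds in earlier trials:* "These studies also used different exercise regimens for their study groups". Those trials gave different regimens to different groups. Here the same patients are observed in both settings during one course of treatment.
- *A reader might carry the point over to the regression of outcomes on adherence under Criterion Validity.* That is a separate question, and no calculation here supports it.

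**Conclusion.** The point holds as a weakness of the stated analysis, not as a demonstrated bias. The test named for home versus clinic cannot separate the setting from the exercises done in it. The article's own expectation about class imbalance supplies one of the two conditions for confounding. The other, unequal mixes, is neither stated nor excluded.

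Under the assumed values, spurious shifts run from 2 to 7.5 points in either direction (the largest is 95% and 70% correct with hard shares of 50% in clinic and 20% at home: −0.30 × 25 = −7.5). A true 5-point advantage of supervision can vanish or change sign. All of this is zero if the mixes match. The change is worth making because it is cheap and brings the test into line with the question asked.

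**What to change.** In Univariable and Multivariable Analyses, give the first Aim 2 hypothesis its own test, made within patient and exercise type and, as a precaution, within the same 2-week interval. Name one of these as primary before the data are analysed:
- for each patient, the mean of the within-exercise, within-interval home-clinic differences, tested with a paired test; or
- a logistic mixed model of the technique call, with exercise type and interval as fixed effects, environment as the tested term, and a random intercept and a random environment slope for patient. A random intercept alone would give too small a standard error if the environment effect varies between patients.

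Keep the crude paired contrast as a secondary analysis. Report the share of home exercise, and of patients, with no matched clinic counterpart.

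The cost is wording. Exercise type is labelled in the clinic and classified at home, and the 2-week interval is already the unit for participation adherence. The sample size need not change, since it was not set for this hypothesis. The small downside is that unmatched home exercise, and patients with little home activity, contribute less to this one test; the secondary analysis and the reported shares make that visible.

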#### Aim 2: Measure the Rate of Adherence to Home Shoulder Physiotherapy, the Relationship Between Adherence and Recovery, and Identify Barriers to Home Physiotherapy Adherence

##### Objectives

The related objectives are as follows:

Inertial sensor data are collected during home physiotherapy for 120 patients with rotator cuff pathology over full treatment duration (up to 5 months).Technical failures preventing home data collection are less than 5%.Clinical outcomes: return to work status, shoulder range of motion, rotator cuff strength, and patient-reported outcomes of pain and disability are collected pretreatment, monthly through treatment (up to 5 months), and at 12-months final follow-up. The final follow-up exceeds 85%.A total of 23 potentially significant predictors of home physiotherapy adherence (identified in Methods: Barriers to Adherence) are collected for all study participants at the time of recruitment.

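### If environment (home or clinic) enters the technique-adherence model, its baseline coefficients average home and clinic effects instead of describing home adherence, and without a patient effect their type I error exceeds 5%

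*Protocol article*

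**What the plan says.** The protocol article (Data Analysis, Univariable and Multivariable Analyses) has a single dependent variable, adherence. It states that "individual baseline adherence predictor variables and environment (home or clinic) will be examined using parametric univariable statistical analyses". The same sentence assigns linear regression to continuous predictors, 2-sample t tests to binary ones and analysis of variance to multiclass ones. Environment is binary, so the test named for it is one for independent groups. The next sentence reads "A multivariable analysis will be conducted to model adherence from statistically significant predictors (maximum 12) and evaluate their relative importance". It gives no model type, unit of analysis or correlation structure.

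Four other places bear on this:

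- Inertial Data Collection requires the watch to be worn for all exercise sessions. "This includes all supervised physiotherapy sessions at the Holland Centre and any physiotherapy exercise sessions conducted by the patient independently (home exercises"). Each patient therefore supplies both clinic and home data.
- The Aim 2 objectives state the target of the barriers work: "A total of 23 potentially significant predictors of home physiotherapy adherence (identified in Methods: Barriers to Adherence) are collected for all study participants" at recruitment. These values are fixed within a patient.
- The first Aim 2 hypothesis is "Exercise technique adherence is better for supervised sessions than at home", at P<.05.
- The section on home participation adherence defines participation by comparing home exercises with those prescribed. It defines no clinic value.

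**The concern.** A factor that varies within patients is placed in the same candidate list, and under the same entry rule, as factors that vary only between patients. Environment can be a predictor only if the dependent variable holds a home value and a clinic value for each patient. For technique both values will exist, and the study's own hypothesis is that environment matters. Following the stated rule could therefore turn the technique barriers model into a model of pooled home and clinic technique.

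Two separate problems would follow:

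1. **Wrong target.** No environment-by-predictor term is mentioned, so each baseline coefficient is an average over the two settings. Aim 2 asks about home.
2. **Wrong error rate.** If the two values per patient are treated as independent, as in the named 2-sample test, each patient counts twice for every baseline predictor.

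At stake is which patient characteristics are reported as barriers to good home technique. The article's discussion of ethical and policy issues says that profiles of patients who do and do not engage could be used in allocating resources.

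**Working it through.** **Inputs from the protocol article.** There are 120 patients, a 5% alpha and the sample size statement: "yields a power of 80% to detect weak correlations (*R*>0.25) between physiotherapy adherence and clinical outcomes". Sidedness is not stated, so two-sided is assumed.

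**Assumptions, not in the article.** Each patient has one home and one clinic technique value with equal variance. Their within-patient correlation rho is taken as 0, 0.2, 0.5 and 0.8. The illustrative barrier is 0.25 SD at home and zero in the clinic.

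**Step 1: the plan's own figure.** Power for R = 0.25 with n = 120 is Phi(sqrt(117) × atanh(0.25) − 1.96) = Phi(10.817 × 0.2554 − 1.96) = Phi(0.80) = 0.789. This agrees with the stated 80%. One-sided testing would give 0.868, which supports the two-sided reading. The figure concerns adherence against clinical outcomes. The article gives none for the barriers model.

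**Step 2: what the pooled model estimates.** With one home and one clinic row per patient and no interaction, the slope of a baseline predictor is (b_home + b_clinic)/2. With b_home = 0.25 and b_clinic = 0 this is 0.125. Rho does not appear in the expression.

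**Step 3: type I error when rows are treated as independent.** The true variance of that slope is (1 + rho) times the variance that ordinary least squares assumes. The actual two-sided error is therefore 2 × (1 − Phi(1.96/sqrt(1 + rho))).

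**Step 4: simulation check.** The pooled model had 240 rows, environment and 12 baseline predictors. The home-only model had 120 rows and the same 12 predictors. There were 3000 runs per rho.

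| rho | Type I, formula | Type I, pooled rows | Type I, home only | Slope, pooled | Slope, home only | Power, pooled | Power, home only |
|---|---|---|---|---|---|---|---|
| 0 | 0.050 | 0.051 | 0.050 | 0.124 | 0.250 | 0.44 | 0.73 |
| 0.2 | 0.074 | 0.070 | 0.050 | 0.125 | 0.250 | 0.46 | 0.71 |
| 0.5 | 0.110 | 0.110 | 0.049 | 0.124 | 0.248 | 0.45 | 0.73 |
| 0.8 | 0.144 | 0.152 | 0.050 | 0.128 | 0.254 | 0.48 | 0.73 |

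**Step 5: are the two problems separate?** Regressing each patient's mean of the two values on the predictors restores the error rate (0.047 to 0.052). Power for the home-only barrier is then 0.44, 0.39, 0.31 and 0.28 across the four values of rho. Correcting for clustering alone therefore does not recover the home effect. An interaction or a home-only outcome is needed.

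**Step 6: the test of environment itself.** Here the unpaired test errs the other way. Its type I error is 2 × (1 − Phi(1.96/sqrt(1 − rho))) = 0.028, 0.006 and below 0.0001 at rho 0.2, 0.5 and 0.8. For a difference of 0.25 SD its power is 0.49, 0.49 and 0.48, against 0.58, 0.78 and 0.99 for a paired test.

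**The case against.** The strongest reply is that the article never says how the multivariable model is fitted. A condensed article may leave model type and correlation structure to a fuller plan. A reader might infer that the barriers model will be fitted to home and clinic rows as if they were independent. The document does not support that as a statement of fact, because independence is explicit only in the univariable tests. The inflation is therefore conditional.

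Other parts of the reply also stand:

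- **Entry is not certain.** Environment must first pass the screen, and Step 6 shows that the unpaired test makes this harder. Hypothesis 1 is an expectation, not a result.
- **Only technique is affected.** Participation has no defined clinic value. A reader might extend the criticism to the whole barriers analysis, but the definition of participation rules that out.
- **Halving is an extreme case.** It assumes no clinic effect at all. A barrier acting equally in both settings is not diluted.
- **The error rates are for a single predictor tested in the pooled model.** They ignore selection by the univariable screen, so they are not the rate at which this plan would declare barriers.
- **The stakes are moderate.** No stated hypothesis concerns barriers, which the article says will be explored. Its program design section names qualitative and knowledge-translation inputs, not this regression.

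The reply does not remove the point that the candidate list, the entry rule and an independent-groups test are all written down. The article does name a paired t test for comparing measurement methods (Concurrent Validity), but none for home against clinic. A later plan that followed this wording would carry the mismatch with Aim 2 forward, even if it added a patient effect.

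**Conclusion.** The point holds as a conditional one about technique adherence. If environment enters the model, the baseline coefficients describe an average of home and clinic rather than home. This needs no assumption about rho. A barrier confined to the home is about halved (0.125 against 0.25 SD), and under the simulated conditions its power falls from roughly 72% to 44-48% with pooled rows.

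The second consequence needs a further condition: that no patient effect is included. Type I error for a null baseline predictor is then about 7%, 11% and 14-15% at rho 0.2, 0.5 and 0.8, against 5%. There is no inflation at rho 0, and the article gives no value for rho.

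The documents do not support a claim that false barriers will in fact be inflated, or that participation barriers are affected.

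**What to change.** In Univariable and Multivariable Analyses, state that the univariable and multivariable barriers analyses use home adherence, with one summary value per patient and with participation and technique modelled separately. The model with at most 12 predictors then rests on up to 120 independent rows. Remove environment from the candidate list. Test it separately, for technique, with a paired (within-patient) comparison as the analysis of Hypothesis 1.

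If home and clinic technique are to stay in one model, specify a patient random intercept and environment-by-predictor terms, and report the home effects as the barriers. A random intercept alone is not enough (Step 5).

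The cost is a short change of wording, with no new data or patients. The one small loss is that environment is no longer ranked for relative importance beside the patient barriers. It keeps its own test, which under a positive home-clinic correlation has more power than the unpaired one.
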